## Aims

The aims of this trial will be to:

i. Test the effectiveness of tailored print-based intervention to improve a) adherence to surveillance colonoscopy recommendations for people with bowel cancer b) adherence to bowel cancer screening guidelines among their first degree relatives.

ii. Examine how the identified cancer patients' and first degree relatives' socio-demographic characteristics, disease characteristics (for index case), risk category (for first degree relatives), intervention groups and providers' characteristics influence whether or not: a) colorectal cancer patients; and b) first degree relatives of colorectal cancer patients, are appropriately screened.

iii. Undertake a cost-effectiveness analysis of the intervention strategy by comparing the differential cost of an intervention and usual care conditions by changes in the quality-adjusted life years associated with each intervention.

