### Statistical analysis

Baseline characteristics of index patients and first degree relatives will be reported for intervention and control groups. *Aim 1*. The proportion of index patients and the proportion of first degree relatives who undertake screening/surveillance tests in line with NHMRC recommendations for their risk category in years 1, 2 and 3 following diagnosis in the index case will be compared between the two experimental groups using the chi-square test. *Aim 2*. Sociodemographic characteristics, screening history, risk status, concurrent engagement in alternative programs of surveillance and symptom status, of those who are appropriately and inappropriately screened at each time point will be compared using the chi-square test for categorical variables and the t-test or a non-parametric equivalent for continuous variables. Logistic regression will then be used to examine factors associated with appropriate screening/surveillance while adjusting for potential confounders. Variables will be included in the initial logistic model if they have a p value of 0.2 or less on univariate analyses, with backward stepwise methods used to exclude variables with a p value of 0.10 or more on the likelihood ratio test. Analysis will be undertaken separately for the index cases and for first degree relatives. Analyses will be adjusted for clustering of relatives within index patients using Generalised Estimating Equations.

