### Sample size

Approximately 3000 eligible new cases of colorectal cancer are expected to be identified through the Victorian Cancer Registry each year. Based on previous experience, 3% of clinicians will refuse permission for their patient to be approached, therefore we expect permission to contact 2900. Based on prior research, we expect 60% of patients contacted by the VCR agree to be contacted by the research team and 70% of these consent to participate in the study. Recruitment will be undertaken for 12 months, thus 1200 index cases will be recruited in total, or 600 per group. *Aim 1*. Assuming that 20% of participants will be lost at each follow-up time (leaving 480, 380, 300 index cases per group available at 12, 24, 36 month), the study will have 80% power, with a 5% significance level, to detect a difference of 10% between experimental groups in the proportion of index cases appropriately surveillance at 12 month follow-up, 12% difference at 24 and 36 month follow-up. It is estimated that there will be an average of 2 eligible first degree relatives for each index case, and that 70% of these will consent and be available for 12 month follow-up, with a 20% loss to follow-up at each of the remaining assessment times. This will provide 1680, 1350 and 1050 relatives at 12, 24 and 36 months. Allowing for a design effect of 2 will provide an effective sample size of 400, 330 and 260 per group at each time point, which is adequate to detect a 10% difference in the proportion of first degree relatives appropriately screened at 12 months, 12% at 24 months and 13% at 36 months with 5% significance level and 80-85% power. A 10% difference at the first follow-up is considered to be clinically meaningful, given the burden of disease from colorectal cancer and the intervention effect is anticipated to increase over time, as the intervention will continue for the three year follow-up period. *Aim 2*. Assuming at least one third of individuals will be appropriately screened at each follow up time, the study will also have at least 80% power to detect differences in characteristics of those who are and are not followed up/screened appropriately of 10-13% for binary variables and 0.2-0.25 standard deviations for continuous variables for index cases, and 11-14% for binary variables and 0.22 -0.27 standard deviations for continuous variables for FDRs.

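### Aim 2 only: p-value selection (univariate 0.2, then backward 0.10) leaves intervals that ignore the selection, does not protect the randomized arm, and pairs a likelihood-ratio test with GEE

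*Protocol article*

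**What the plan says.** All references are to the protocol article. Under Statistical analysis, the Aim 2 model has an explanatory purpose: "Logistic regression will then be used to examine factors associated with appropriate screening/surveillance while adjusting for potential confounders". Its content is decided in two steps. The first is "Variables will be included in the initial logistic model if they have a p value of 0.2 or less on univariate analyses"; the second is "with backward stepwise methods used to exclude variables with a p value of 0.10 or more on the likelihood ratio test". The characteristics to be compared beforehand are "Sociodemographic characteristics, screening history, risk status, concurrent engagement in alternative programs of surveillance and symptom status", at each time point. Index cases and relatives are analysed separately, with GEE to allow for clustering of relatives within index patients.

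Under Aims, the second aim covers socio-demographic factors, disease characteristics for the index case and risk category for relatives. It continues with "intervention groups and providers' characteristics influence whether or not" patients and relatives are appropriately screened. Intervention group is therefore one of the factors to be examined.

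Under Sample size, Aim 2 is planned with "Assuming at least one third of individuals will be appropriately screened at each follow up time".

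**The concern.** The aim names its factors in advance, but the analysis lets each stay or go on its own p value. Four things follow.

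- A factor that the aim promises to examine, the randomized arm included, can end without an adjusted estimate.
- A confounder with p of 0.10 or more is removed however far it shifts the other coefficients.
- The final intervals are computed as if the model had been fixed beforehand.
- Selection is repeated at three time points in two samples, so up to six adjustment sets may differ and their odds ratios would not be comparable.

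There is also a technical mismatch. Removal is by likelihood ratio test, but GEE has no full likelihood, so that test does not carry over directly to the relatives' model.

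At stake is the reliability of Aim 2's product, a list of factors with odds ratios.

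**Working it through.** **1. Inputs.** From Sample size: index cases 480, 380 and 300 per group (960, 760 and 600 in all) at 12, 24 and 36 months; relatives 400, 330 and 260 effective per group after a design effect of 2 (800, 660 and 520); one third appropriately screened; 5% significance, taken as two-sided. From Statistical analysis: thresholds 0.20 and 0.10. Not given, so assumed: number of candidates, effect sizes and correlations.

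**2. The plan's own Aim 2 figures.** With n1 = N/3 and n2 = 2N/3, the detectable difference in SD is (1.96 + 0.84) × sqrt(1/n1 + 1/n2). For N = 960 this is 2.80 × sqrt(1/320 + 1/640) = 0.192. The worst-case binary difference is about half of it.

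| Sample | SD at 12, 24, 36 months | Stated | Binary, points | Stated |
|---|---|---|---|---|
| Index cases | 0.192, 0.216, 0.243 | 0.20-0.25 | 9.6, 10.8, 12.1 | 10-13 |
| Relatives | 0.210, 0.231, 0.261 | 0.22-0.27 | 10.5, 11.6, 13.0 | 11-14 |

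The figures reproduce, slightly conservatively. They describe simple two-group comparisons, not coefficients left after selection.

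**3. Chance that the arm fails the 0.10 threshold.** With m per group and true difference d, z = d / sqrt(2 × (1/3)(2/3)/m), and P(p ≥ 0.10) = Φ(1.645 − z) − Φ(−1.645 − z). For m = 480 and d = 0.05, z = 0.05/0.0304 = 1.64 and P = 0.50.

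| Sample, month | m | No effect | 5 points | Planned difference |
|---|---|---|---|---|
| Index, 12 | 480 | 90% | 50% | 5% (10 points) |
| Index, 24 | 380 | 90% | 57% | 3% (12 points) |
| Index, 36 | 300 | 90% | 63% | 7% (12 points) |
| Relatives, 12 | 400 | 90% | 56% | 9% (10 points) |
| Relatives, 24 | 330 | 90% | 61% | 5% (12 points) |
| Relatives, 36 | 260 | 90% | 67% | 7% (13 points) |

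**4. Simulation of the stated rule.** Likelihood-ratio screening at 0.20, then backward removal at 0.10, against the full model. Besides the arm, four real covariates had log-odds 0.30, 0.15, 0.15 and 0.10; correlation was 0.3, with 1000 runs per setting. Arm log-odds were 0, 0.22 (about 5 points) and 0.44 (about 10 points). Relatives are represented by their effective size, without simulated clustering.

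| N, candidates | Coverage, all retained | Retained null | Retained real | Full model | Arm dropped at 0 / 0.22 / 0.44 |
|---|---|---|---|---|---|
| 960, 15 | 82.5-86.1% | 37.7-43.5% | 95.4-95.7% | 95.0-95.2% | 89.5 / 51.8 / 6.6% |
| 600, 15 | 78.2-83.1% | 39.3-41.3% | 94.6-95.7% | 94.7-94.8% | 89.7 / 65.5 / 21.1% |
| 520, 17 | 73.4-79.7% | 39.7-40.2% | 93.7-95.7% | 94.2-94.9% | 89.6 / 66.8 / 28.3% |

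A separate simulation with 15 candidates gave 82-87% for retained terms against 95% in the full model, and dropped an arm with a true effect of about 5 points in 58-68% of runs.

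The low figure for null terms has a simple source. At N = 960 with no arm effect, a null term was retained in 8.1% of runs and retained with p below 0.05 in 4.6%, so its coverage given retention is about 1 − 4.6/8.1 = 43%.

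**5. Overstatement of retained real effects.** Mean estimate divided by truth, when retained:

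| Log-odds per SD | N = 960 | N = 600 | N = 520 |
|---|---|---|---|
| 0.30 | 1.00-1.01 | 1.03-1.04 | 1.05-1.06 |
| 0.15 | 1.25-1.29 | 1.47-1.51 | 1.57-1.60 |
| 0.10 | 1.66-1.73 | 2.03-2.08 | 2.12-2.23 |

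Further runs at N = 960 with other effect patterns gave about 25% overstatement at 0.175, 7% at 0.25 and 3% at 0.30.

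**6. Model size that the data can carry.** Events = N/3.

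| Sample | Events at 12, 24, 36 months | Parameters at 10 events each | At 20 each |
|---|---|---|---|
| Index cases | 320, 253, 200 | 32, 25, 20 | 16, 12, 10 |
| Relatives (effective) | 267, 220, 173 | 26, 22, 17 | 13, 11, 8 |

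The Background's lowest adherence figure is 23%, reported for surveillance colonoscopy. Applied to relatives at 36 months purely as an illustration, it leaves 520 × 0.23 ≈ 120 events, or about 12 parameters at 10 each.

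**The case against.** The best defence is that this is a secondary, associational aim and that the treatment question is answered elsewhere. Under Aim 1 the proportions adherent "will be compared between the two experimental groups using the chi-square test", and Aim 2 selection cannot touch that test. A reader might infer that the trial's conclusion about the intervention is at risk; the article does not support that. Nor does it say that the arm is put through the screen: the Aim 2 list of compared characteristics omits it, and a fuller plan could force it in. What stands is that the second aim names the arm and the published rule contains no exception for it.

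A second defence is that the intervals are not generally too short. Retained real terms kept 94-96% coverage, and a null term was falsely declared significant at about the usual rate overall (4.4-5.7%). This is correct and narrows the point. The shortfall appears once attention is confined to retained terms, but that is the list Aim 2 would report, and the reader cannot tell which entries are noise.

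Third, the size of the exaggeration depends on assumed effects and nearly vanishes for strong ones. That also stands.

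Fourth, it would be too strong to say that a confounder visible only jointly never enters: a marginally null variable passes the 0.2 screen about 20% of the time. Usually, though, it is left out.

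Finally, the article names classes of factor rather than a parameter count, so it cannot be said flatly that the sample supports any full model. Relatives at 36 months are the tight case.

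**Conclusion.** The point holds for Aim 2, as a moderate one. The stated rule does not suit a model meant to adjust for confounders, and it leaves a factor named in the aim unprotected. Coverage of retained terms falls to about 73-87% against about 95%, driven mainly by null terms. Overstatement is material for weak effects and larger at smaller N, but slight for strong ones. An arm with a true effect of about 5 points would be dropped in roughly half to two thirds of cases. At the planned differences the approximation in step 3 gives 3-9%.

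The direction follows from selection that the intervals ignore. The sizes rest on the assumed 15 to 17 candidates, correlation of 0.3 and effect sizes. The mismatch between likelihood-ratio removal and GEE rests on the text alone.

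The evidence does not show that every retained effect is exaggerated, that every interval is too narrow, or that the Aim 1 result is compromised.

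**What to change.** For each sample and each time point, fit one pre-specified logistic model, using GEE with robust intervals for relatives. Always include intervention group, the collected factors named in the second aim, and those listed under Statistical analysis: screening history, risk status, concurrent alternative surveillance and symptom status. Use no p-value entry or removal. Report every coefficient with its interval, and keep the univariate tables as description. This also removes the need for a likelihood ratio test under GEE.

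Set the number of parameters in advance from the expected events: roughly 20-32 for index cases and 17-26 for relatives at 10 events each, depending on the time point. State beforehand which categories will be grouped if adherence is below one third.

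The cost is a change of analysis wording and slightly wider intervals. No further data are needed for the factors already collected.

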### Sample size

Approximately 3000 eligible new cases of colorectal cancer are expected to be identified through the Victorian Cancer Registry each year. Based on previous experience, 3% of clinicians will refuse permission for their patient to be approached, therefore we expect permission to contact 2900. Based on prior research, we expect 60% of patients contacted by the VCR agree to be contacted by the research team and 70% of these consent to participate in the study. Recruitment will be undertaken for 12 months, thus 1200 index cases will be recruited in total, or 600 per group. *Aim 1*. Assuming that 20% of participants will be lost at each follow-up time (leaving 480, 380, 300 index cases per group available at 12, 24, 36 month), the study will have 80% power, with a 5% significance level, to detect a difference of 10% between experimental groups in the proportion of index cases appropriately surveillance at 12 month follow-up, 12% difference at 24 and 36 month follow-up. It is estimated that there will be an average of 2 eligible first degree relatives for each index case, and that 70% of these will consent and be available for 12 month follow-up, with a 20% loss to follow-up at each of the remaining assessment times. This will provide 1680, 1350 and 1050 relatives at 12, 24 and 36 months. Allowing for a design effect of 2 will provide an effective sample size of 400, 330 and 260 per group at each time point, which is adequate to detect a 10% difference in the proportion of first degree relatives appropriately screened at 12 months, 12% at 24 months and 13% at 36 months with 5% significance level and 80-85% power. A 10% difference at the first follow-up is considered to be clinically meaningful, given the burden of disease from colorectal cancer and the intervention effect is anticipated to increase over time, as the intervention will continue for the three year follow-up period. *Aim 2*. Assuming at least one third of individuals will be appropriately screened at each follow up time, the study will also have at least 80% power to detect differences in characteristics of those who are and are not followed up/screened appropriately of 10-13% for binary variables and 0.2-0.25 standard deviations for continuous variables for index cases, and 11-14% for binary variables and 0.22 -0.27 standard deviations for continuous variables for FDRs.

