### Follow up assessments

Both first degree relatives and patients will be mailed follow up surveys at 12, 24 and 36 months. First degree relatives will be asked to provide self report information on the type of bowel cancer screening undertaken in the past 12 months (if any), and any days off work due screening. Patients will be asked to provide self report information about participation in surveillance colonoscopy within the past 12 months, quality of life. Patients or first degree relatives who report having had a colonoscopy or bowel cancer screening test in the past 12 months will be asked for permission to contact their doctor to verify the timing and results of the test. A random sample of 10% of self reported screening will be verified in this way to determine accuracy of self reported screening behavior.

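### Aim 1 is tested by a separate chi-square each year on outcomes known only from returned surveys; with half the index cases expected lost by 36 months, arm-specific selective response could supply a sizeable part of the target difference

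*Protocol article*

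**What the plan says.** The Statistical analysis section of the protocol article fixes the Aim 1 test. The proportions acting in line with the guideline "in years 1, 2 and 3 following diagnosis in the index case will be compared between the two experimental groups using the chi-square test". The section's closing sentence provides Generalised Estimating Equations (GEE) for relatives clustered within index patients. That deals with correlation, not with non-response.

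The Follow up assessments section gives the source of the outcome: "Both first degree relatives and patients will be mailed follow up surveys at 12, 24 and 36 months". For patients the recall window is one year: "Patients will be asked to provide self report information about participation in surveillance colonoscopy within the past 12 months". A missed survey therefore leaves that year unknown, and the next survey does not ask about it. Doctors are contacted only to verify a 10% random sample of self-reported tests, which gives no information on people who did not reply.

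The Sample size section starts from 1200 index cases ("thus 1200 index cases will be recruited in total, or 600 per group") and then applies attrition: "Assuming that 20% of participants will be lost at each follow-up time (leaving 480, 380, 300 index cases per group available". Power is claimed on those reduced numbers: "the study will have 80% power, with a 5% significance level, to detect a difference of 10% between experimental groups", with 12 points as the target at 24 and 36 months.

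**The concern.** The named test takes a yes/no outcome and an arm, and nothing else. Applied to survey-only outcomes, it can include only people who replied at that wave unless some rule fills in the rest, and the article states none. The baseline interviews collect screening history, intentions and family-history risk, all plausible predictors of both adherence and reply, but a chi-square cannot use them. Nor can it use what an earlier survey showed about someone who later drops out.

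The arms could plausibly differ in who replies. Intervention patients and relatives are told what is recommended for them, and their doctors are written to; controls receive generic material. People who know that they have followed, or not followed, explicit advice may return a survey about it at different rates. With about half of the outcomes missing at 36 months, such a pattern could create, inflate or hide a difference, and a larger sample would not correct it.

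**Working it through.** **Inputs from the article.** 600 index cases per group; 20% loss per wave; 480, 380 and 300 left; targets of 10 points at 12 months and 12 points at 24 and 36 months; 5% significance (two-sided assumed). Two adherence levels appear: 23% to 38% in the Background and at least one third in the Aim 2 power statement.

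**Assumptions, not in the article.** The size of any response gap (5, 10 or 15 points), and an upper adherence value of 50%.

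**1. The plan's own figures.** 600 × 0.8 = 480; 600 × 0.8² = 384; 600 × 0.8³ = 307. The stated 480, 380 and 300 agree within 3%. Loss by 36 months is 48.8% exactly, or 50% on the stated figures. At the least favourable proportions (near 50%), power is 87% (10 points, 480 per group), 91% (12 points, 380) and 84% (12 points, 300). The 80% claim is met, so sample size is not the problem.

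**2. Bias formula.** Let true adherence be *p* in both arms (no effect). In the control arm, reply does not depend on adherence. In the intervention arm adherers reply at rate *r1* and non-adherers at *r0* = *r1* − *d*, with overall response held at *R*. Then

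observed proportion = *p·r1* / (*p·r1* + (1 − *p*)·*r0*) = *p·r1* / *R*.

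Since *r1* = *R* + (1 − *p*)*d*, the spurious difference is **p(1 − p)d / R**.

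**3. At 36 months, R = 0.50 (300/600).**

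| Gap *d* | *p* = 0.23 | *p* = 1/3 | *p* = 0.50 | Share of 12 points (*p* 0.23 to 0.50) |
|---|---|---|---|---|
| 5 points | 1.8 | 2.2 | 2.5 | 15–21% |
| 10 points | 3.5 | 4.4 | 5.0 | 30–42% |
| 15 points | 5.3 | 6.7 | 7.5 | 44–62% |

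Example: *p* = 1/3, *d* = 0.10 gives *r1* = 0.567 and *r0* = 0.467. The observed proportion is 0.333 × 0.567 / 0.50 = 0.378 against 0.333, or 4.4 points. With 300 per group, the chance of a significant result favouring the intervention is then about 20%, against a nominal 2.5% in that direction.

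**4. Earlier waves, 10-point gap, p = 0.23 to 0.50.** At 12 months (*R* = 0.80) the bias is 2.2 to 3.1 points, 22–31% of the 10-point target. At 24 months (*R* = 0.64) it is 2.8 to 3.9 points, 23–33% of 12.

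**5. Patterns that do little harm.** If *r1* and *r0* are the same in both arms, equal true proportions give equal observed proportions, so the bias under the null is zero; a true 12-point effect would appear as about 11 to 14 points. If overall response is 45% in one arm and 55% in the other, and repliers are 10 to 30 points more adherent than non-repliers in both, the bias is (0.55 − 0.45) × 10 to 30 = 1 to 3 points.

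**6. Counting non-repliers as not adherent.** In the example of step 3 the arms become 0.333 × 0.567 = 18.9% and 0.333 × 0.50 = 16.7%. The spurious difference falls to 2.2 points but does not vanish. A true 33% against 45% would shrink to 17% against 23% of 600 per group, with power of about 74%.

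**The case against.** The strongest objection is that a condensed article names a test and leaves missing data to the full protocol or the SAP, and that discounting a sample size for attrition does not define an analysis set. This is partly right. A reader might infer that the article prescribes a respondents-only analysis; it does not say so, and an unseen SAP could define the population. What stands is narrower: the test that is named, on survey-only outcomes and sized on those available, has no means of using the other data collected.

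A reader might also infer that the test is valid only if reply is unrelated to adherence. That is too strong: step 5 shows no bias under the null when the dependence is the same in both arms.

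Nor do the figures support saying that selection could match the target. The worked scenarios stay below two thirds of it, and they put the whole gap in one arm and none in the other. Controls also receive bowel cancer material, so a zero gap there is a simplification. The 12-month comparison, which the article ties to clinical importance, is less exposed. The half-lost figure applies to index cases only; the 13-point target at 36 months belongs to relatives.

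Finally, baseline data are not wholly unused. Aim ii lists intervention group among its factors, and the Aim 2 logistic regression adjusts for confounders. But that model selects variables by p-value to find predictors of adherence; the between-arm test stated for Aim 1 remains the chi-square.

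**Conclusion.** The concern holds as a weakness of the stated Aim 1 test, not as a missing section and not as evidence that the result will be biased. With 50% response at 36 months, no true effect and adherence of 23% to 50%, an adherence-related response gap of 5 to 15 points in one arm only produces a spurious difference of about 2 to 7.5 points, 15% to 62% of the 12-point target. This rests on response depending on adherence differently by arm and on gap sizes that are assumed. The gap could run in either direction, so a real effect could equally be masked. The change is worth making because the exposure is large at the later waves and the data needed are already being collected.

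**What to change.** Keep a separate arm contrast for each year, since each survey covers its own 12 months, but change how it is estimated:

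- **Main analysis:** a logistic model adjusted for baseline screening history, intentions and risk category, with GEE clustered by family for relatives. Combine it with multiple imputation, or with inverse-probability-of-response weighting, using baseline and earlier-wave data. GEE on the observed records alone would not remove outcome-related non-response.
- **Secondary analysis:** the chi-square among those with data, labelled as such.
- **Sensitivity analysis:** vary the response gap between adherers and non-adherers separately in each arm (for example 0 to 15 points) and report where the conclusion changes. Counting non-repliers as not adherent can be one crude scenario, not the safeguard (step 6 of the working).
- **Reporting:** response by arm and wave, with deaths separate from non-response.

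The cost is analysis wording and modest programming; recruitment and data collection do not change. The main estimate would still assume that the recorded variables explain response, which is why the arm-specific sensitivity analysis is needed.
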